## Methods

### Design

The PROTECTION (Pressure support ventilation + sigh in acute hypoxemic respiratory failure patients) trial is an investigator-initiated, international, multicenter, parallel randomized controlled two-arm trial that will be performed in intubated and ventilated patients with AHRF, who are admitted to the intensive care unit (ICU). The study will be conducted in adherence to the principles of the World Medical Association’s Declaration of Helsinki and in accordance with the Medical Research Involving Human Subjects Act (WMO). Ethics approval will be sought from each participating institution before starting enrollment and consent will be obtained for each patient following local regulations. The Institutional Review Board of the coordinating center approved the protcol on 12 June 2017 under reference number 318_2017bis. The trial was registered at www.clinicaltrials.gov with code NCT03201263 in June 2017. The Standard protocol items: recommendation for interventional trials (SPIRIT) checklist can be found in Additional file 1 and the SPIRIT figure is included in the main body of the manuscript (Fig. 1).

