### Randomization

At the end of the sigh test, patients will be randomized through an online automatic centralized and computerized system to one of the two study groups (1:1 ratio): PSV or PSV + sigh. Due to the nature of the intervention, blinding will not be feasible.

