### Data collection

At enrollment, before the sigh test we will anonymously collect patients’ demographic information (e.g., age, sex, height, weight), past (e.g., hypertension, chronic medications) and recent (e.g., etiology of the acute respiratory failure, days since intubation) medical history, severity of lung injury (e.g., ventilation setting, arterial blood gases, respiratory system compliance, diagnosis of acute respiratory distress syndrome (ARDS)) and of systemic involvement (e.g., presence of shock, number of organ failures) and finally, ventilation data (e.g., RR, Vt, PEEP, FiO_2_, PSV level).

In both groups, for the first 24 h, we will assess the SpO_2_/FiO_2_ ratio, RR and PSV tidal volume every 4 h to further characterize physiologic response to sigh over time.

From day 1 (i.e., within 24 h from randomization) to day 28 or death or discharge from the ICU, the following data will be collected every day between 6:00 and 10:00 in the morning: arterial SpO_2_, arterial and central venous blood gas analyses, ventilation settings and pattern (i.e., sigh pressure level, sigh tidal volume, PSV level, PSV tidal volume, respiratory rate, PEEP, FiO_2_, minute ventilation, P0.1, mean airway pressure), heart rate, arterial blood pressure, central venous pressure, cumulative fluid balance, patient’s comfort assessed using a visual analog scale (VAS), RASS value, SOFA score and dosage of sedative agents and vaso-active drugs.

Moreover, each day we will collect information on use of rescue treatments (i.e., recruitment manoeuvers, use of PEEP ≥ 15 cmH_2_O, prone positioning, inhaled nitric oxide, extracorporeal membrane oxygenation), tracheostomy, switch from the allocated treatment to the other study arm for ≥ 24 h, switch to controlled ventilation for ≥ 24 h, reason for switch to controlled ventilation, adverse events (i.e., hemodynamic instability with hypotension with SBP < 90 mmHg despite vasoactive drugs; arrhythmias; radiographic evidence of barotrauma with pneumothorax, pneumomediastinum, pneumatocoele, or subcutaneous emphysema), SBT performance and reason for SBT failure, extubation or separation from mechanical ventilation, reintubation and reason for reintubation with time. We will collect data on day 28 for all enrolled patients on mortality, extubation that occurred outside the ICU and readmission to ICU.

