### Statistical analysis

Continuous normally distributed variables will be expressed by their mean and standard deviation or as medians and their interquartile ranges when not normally distributed. Categorical variables will be expressed as number and proportion (%). To assess the feasibility of PSV + sigh as compared to PSV (i.e., the primary endpoint), we will compute the proportion of patients experiencing at least one of the following events in each arm: switch to controlled ventilation for ≥ 24 h consecutively; use of PEEP ≥ 15 cmH2O, prone positioning, inhaled nitric oxide, extracorporeal membrane oxygenation or reintubation within 48 h from extubation.

We will compare the two proportions using the one-tailed non-inferiority test for proportions with a 5% tolerance. We will use 0.05 as the significance level. The same method will be adopted to evaluate the safety of PSV + sigh, which is a secondary endpoint. Prevalence of sigh responders in the two arms will be compared using the chi-squared or Fisher’s exact test. Ventilator-free days will be calculated as the difference between the duration of follow up (up to 28 days) and the number of days of intubation before successful extubation or separation from mechanical ventilation for tracheostomized patients. For all the secondary endpoints, we will use the chi-squared or Fisher’s exact test in the case of binary variables or the *t* test or Wilcoxon signed rank test for continuous variables. Time to death or extubation will be analyzed using Kaplan-Meier survival curves. Adjustement for potential confounding factors will be evaluated using appropriated regression models.

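### The protocol names the Wilcoxon signed rank test, a paired test, for comparing continuous secondary endpoints between two independent arms; the rank-sum test is almost certainly meant

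*Protocol article*

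**What the plan says.** The Statistical analysis section of the protocol article sets the tests for secondary endpoints in one sentence. It opens "For all the secondary endpoints, we will use the chi-squared or Fisher’s exact test in the case of binary variables" and continues with the t test or "Wilcoxon signed rank test for continuous variables". The same section summarises continuous variables by mean and standard deviation, or "as medians and their interquartile ranges when not normally distributed". It does not say outright that the Wilcoxon test is for the non-normal case. That follows from its pairing with the t test and from this summary rule.

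The Design section describes a "multicenter, parallel randomized controlled two-arm trial". The Randomization section allocates patients to "one of the two study groups (1:1 ratio): PSV or PSV + sigh" and mentions no matching. The Secondary endpoints section has the listed variables compared between the two groups, first in everyone and then only in patients whose oxygenation improved in the pre-randomisation sigh test. The continuous or count variables listed there include ventilator-free days, days on assisted ventilation, ICU and hospital length of stay, PSV level, PEEP and oxygenation index on days 1 to 3, and chest x-ray quadrants.

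**The concern.** The signed rank test ranks within-pair differences. Patients in two independently randomised arms form no pairs, so the named procedure has no natural input. An analyst who follows the sentence literally must either stop, because the arms differ in size, or pair patients by whatever order the data file happens to have.

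What is at stake is the pre-specification of the non-parametric comparison for every continuous secondary endpoint. Durations such as ventilator-free days and length of stay are commonly skewed (an assumption here, since the document gives no distributions), so the non-parametric option is likely to be used. The Discussion says the planned larger trial will use a composite of 28-day survival and ventilator-free days. The pilot's ventilator-free-day comparison is therefore one that later planning would draw on.

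**Working it through.** **1. Is there any paired continuous comparison the name could serve?** None is described. The short-term and long-term responses to sigh are within-patient, but the Sigh test and Secondary endpoints sections turn them into responder status, a binary variable. The Statistical analysis section compares its prevalence by chi-squared or Fisher's exact test. Safety uses the non-inferiority test for proportions. The Wilcoxon test is left only for between-arm comparisons.

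**2. Is the primary analysis affected?** Inputs from the Sample size and Statistical analysis sections: failure 22% (PSV) and 15% (PSV + sigh), tolerance 5 percentage points, one-sided alpha 0.05, power 0.80.

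n per arm = (1.645 + 0.842)² × (0.22 × 0.78 + 0.15 × 0.85) / (0.05 + 0.07)² = 6.18 × 0.2991 / 0.0144 ≈ 128.4, rounded up to 129.

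This reproduces the stated 129 per arm (258 in total). It rests on a binary endpoint and does not involve the Wilcoxon test.

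**3. Unequal arms.** The signed rank routine returned an error with 131 and 127 patients. Equal counts in the responder-only analyses would be chance, since the Randomization section mentions no stratification by responder status. With 129 per arm and responder rate p (assumed), the chance of equal counts is about 1/√(2π × 2 × 129 × p(1 − p)):
- p = 0.5: 1/√(2π × 64.5) ≈ 5%
- p = 0.3 or 0.7: 1/√(2π × 54.18) ≈ 5%
- p = 0.1 or 0.9: 1/√(2π × 23.22) ≈ 8%

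Comparisons on days 1 to 3 can also lose patients to extubation or death, in differing numbers per arm.

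**4. Equal arms: dependence on row order.** One simulated lognormal data set was used, with 129 per arm, log-scale SD 1 and a log-scale shift of 0.25 (all assumed). The rank-sum test gave one value, p = 0.0011. Over 2000 random pairings the signed rank p-value ran from 0.000003 to 0.022 (central 95%: 0.0002 to 0.0082). In a second skewed data set, rank-sum gave 0.056 and signed rank about 0.06 to 0.31 (central 95%). All 2000 pairings in the first example fell below 0.05, and the central range of the second lay above it. The examples therefore show an arbitrary p-value, not a conclusion that readily flips.

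**5. Type I error.** If the two distributions are identical and the pairing is unrelated to outcome, the paired differences are symmetric about zero, so the signed rank test keeps its size. Simulated signed rank rates ranged from 4.75% to 5.7%; rank-sum gave 4.75% and 5.3% in two of the same sets of runs. With 4000 runs the simulation standard error is √(0.05 × 0.95/4000) ≈ 0.34 percentage points, so even 5.7% is only about two standard errors from 5%.

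**6. Power** (129 per arm, two-sided 5%; every shape and effect is assumed; ranges are over repeated sets of runs):

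| Assumed outcome | Rank-sum | Signed rank, arbitrary pairs |
|---|---|---|
| Exponential, 0.25 SD shift | 85–88% | 66–68% |
| Lognormal, 0.35 SD log shift | 76–78% | 72–73% |
| Normal, 0.25 SD shift | 50–51% | 50–51% |
| Exponential, 1.4-fold scale change | 65–66% | 69–70% |

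The difference runs from about 20 points in favour of rank-sum to about 4 points against it.

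**The case against.** The best reply is that this is a slip in naming. The test stands beside the t test and the chi-squared test, in a sentence about comparing two groups. Software would refuse unequal arms, so an analyst would probably notice and use the rank-sum test. That is likely, and it limits the practical harm to an ambiguous pre-specification. It does not make the published sentence right. Nor is this a detail left to an unseen analysis plan, because the article names a specific test and that test does not fit the design.

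A reader might go further than the documents allow in three ways:
- **Invalid, in the sense of too many false positives.** Not supported: size stays near 5% when the pairing is unrelated to outcome. Not applicable to independent arms, and arbitrary if forced, is the accurate description.
- **A general loss of power on skewed outcomes.** Not supported: the ordering reverses for an exponential scale change, and the document gives no distribution or effect size for these endpoints.
- **An error in not adjusting PSV level and PEEP on days 1 to 3 for enrolment values.** Not supported. The Data collection section does record "ventilation data (e.g., RR, Vt, PEEP" and PSV level at enrolment. But an unadjusted comparison is valid under randomisation, and the Statistical analysis section already leaves room for regression adjustment.

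**Conclusion.** The point holds as a wrong statement with a narrow reach. The named test requires pairs that the design does not have. It cannot be run on unequal arms, and on equal arms it gives a p-value set partly by row order. It concerns only continuous secondary endpoints, in the whole population and among responders. The primary endpoint, the binary secondary endpoints, the safety comparison and the sample size are untouched.

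The mismatch itself needs no assumption, because it follows from the Design, Randomization, Secondary endpoints and Statistical analysis sections read together. The illustrative sizes do rest on assumptions: the simulated shapes and shifts, and the responder rate behind the 5 to 8% chance of equal counts. That the rank-sum test was meant is a reading of the context, not something the document states. The correction should be made, but it does not threaten the trial's main conclusion.

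**What to change.** In the Statistical analysis section, replace the signed rank test with the Wilcoxon rank-sum (Mann-Whitney) test, and state that it applies to continuous secondary endpoints that are not normally distributed. This changes one term and adds a short qualifier. No new data are needed and the sample size stays the same.

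Optionally, to gain precision rather than to correct an error, specify that PSV level and PEEP on days 1 to 3 are compared with adjustment for the enrolment values already collected, within the regression models the section already allows.

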### Interventions: ventilation strategies for each study arm

#### PSV group

After randomization, clinicians will set PSV to meet the following targets: tidal volume (Vt) of 6–8 mL/kg of predicted body weight (PBW), with respiratory rate (RR) 20–35 bpm. FiO_2_ will be left as selected before the pre-randomization sigh test, while PEEP will be left as clinically set.

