#### Secondary endpoints

The study will also provide a preliminary evaluation of the safety of PSV + sigh by comparing the incidence of the following adverse events in the two study groups: hemodynamic instability with hypotension (i.e., SBP < 90 mmHg) despite vasoactive drugs; arrhythmias with heart rate < 40 or > 140 bpm; radiographic evidence of barotrauma (i.e., pneumothorax, pneumomediastinum, pneumatocoele or subcutaneous emphysema or new chest tube placement.

Furthermore, it will quantify the prevalence of short-term (i.e., within 30 min) and long-term (i.e., within 24 h in the PSV + sigh group) sigh responders defined by improved oxygenation. Finally, it will assess the following clinical outcomes: 28-day mortality; ventilator-free days; PSV level, PEEP value and oxygenation index on day 1–3; number of days on assisted ventilation until day 28; use of rescue treatments; number of quadrants involved on chest x-ray on day 1–5; ICU and hospital length of stay and tracheostomies. The listed variables will be analyzed by comparing the two study groups considering, first, the whole study population and, then, only patients who improved oxygenation during the pre-randomization sigh test (sigh responders).

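### PSV level, PEEP and oxygenation index on days 1–3 are compared without their pre-randomisation values: a valid analysis, but one that gives up precision at no saving

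*Protocol article*

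**What the plan says.** Secondary endpoints names "PSV level, PEEP value and oxygenation index on day 1–3" and sets out the comparison: "The listed variables will be analyzed by comparing the two study groups considering, first, the whole study population", followed by sigh responders only.

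Statistical analysis fixes the method by type of variable. The rule opens "For all the secondary endpoints, we will use the chi-squared or Fisher’s exact test in the case of binary variables" and goes on to give continuous variables a t test or "Wilcoxon signed rank test for continuous variables". No baseline value, change score or covariate is mentioned. The section closes with a general sentence: "Adjustement for potential confounding factors will be evaluated using appropriated regression models".

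Data collection lists what is known at entry. It begins "At enrollment, before the sigh test we will anonymously collect" and includes arterial blood gases and "ventilation data (e.g., RR, Vt, PEEP, FiO_2_, PSV level". Randomisation follows the sigh test, so all of this precedes allocation. Mean airway pressure is named only in the daily record that starts on day 1.

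After randomisation, the PSV group section says "PEEP will be left as clinically set", and the PSV + sigh section likewise keeps clinical PEEP. Pressure support, in contrast, is set to tidal volume and respiratory rate targets in both arms. Under Adjusting ventilation settings, PSV and PEEP then move in 2 cmH2O steps, with eight hours as the longest interval between adjustments.

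**The concern.** A patient's PEEP on day 1 depends partly on the PEEP with which that patient entered, and entry PEEP may lie anywhere from 5 to just under 15 cmH2O. A two-group test on follow-up values treats that inherited spread as noise. The confidence interval is then wider than necessary, and the point estimate includes whatever baseline difference chance has produced between the arms.

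This matters because the trial is a pilot for a larger one, and its Discussion relies on the physiological data to reconstruct how sigh acts. An imprecise early comparison of ventilator settings and oxygenation is less useful for both purposes.

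**Working it through.** **The plan's own figure.** The document gives a sample size for the primary endpoint only. On the success scale (0.78 vs 0.85), with margin 0.05, one-sided alpha 0.05 and power 0.80:

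n per arm = (1.645 + 0.842)² × (0.78×0.22 + 0.85×0.15) / (0.07 + 0.05)² = 128.4, rounded up to 129.

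This reproduces the stated 129 per arm. Nothing below alters it.

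**Inputs for the days 1–3 endpoints.** From the document: 129 per arm, 1:1 allocation. Assumed, because the document is silent: a two-sided 5% test, a true difference of 0.25 SD, a value for every patient, and a correlation rho between the baseline and follow-up value.

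**Formulas.** Standard error of the unadjusted difference, in SD units: √(2/129) = 0.1245. Adding the baseline value as covariate multiplies the variance by 1 − rho². Power = Φ(0.25 / (0.1245 × √(1 − rho²)) − 1.96). Difference detectable at 80% power = (1.96 + 0.842) × 0.1245 × √(1 − rho²). Equivalent unadjusted size per arm = 129 / (1 − rho²).

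| rho | variance factor | detectable difference (SD) | power at 0.25 SD | equivalent n per arm |
|---|---|---|---|---|
| unadjusted | 1.00 | 0.349 | 52% | 129 |
| 0.3 | 0.91 | 0.333 | 56% | 142 |
| 0.5 | 0.75 | 0.302 | 64% | 172 |
| 0.7 | 0.51 | 0.249 | 80% | 253 |

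A simulation of t test against ANCOVA (3000 runs per rho) gave 52% vs 55%, 51% vs 62% and 52% vs 80% at rho 0.3, 0.5 and 0.7, in line with the formula.

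**How rho might behave for PEEP.** This is an illustration on assumed inputs. Take entry PEEP as uniform on the integers 5 to 14 (variance (10² − 1)/12 = 8.25), with a review every 8 h and a probability q of a 2 cmH2O step up and the same probability down. Each review adds variance 2 × q × 2² = 8q, so after k reviews rho = √(8.25 / (8.25 + 8qk)).

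| time | k | rho at q = 0.1 | rho at q = 0.3 |
|---|---|---|---|
| 24 h | 3 | 0.88 | 0.73 |
| 48 h | 6 | 0.79 | 0.60 |
| 72 h | 9 | 0.73 | 0.53 |

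At 72 h baseline explains 0.73² = 53% down to 0.53² = 28% of the variance. Confining PEEP to 5–15 gives 0.72 down to about 0.42 at 72 h. The correlation falls with time, and more frequent adjustment would lower it further. At one step per eight hours a setting can move 3 × 2 = 6 cmH2O in 24 h and 9 × 2 = 18 cmH2O in 72 h, so the small step size does not by itself guarantee a high correlation on days 2 and 3.

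**The case against.** The strongest reply is that nothing here is an error. In a randomised trial an unadjusted comparison holds its type I error, and its interval already allows for chance imbalance. That stands, and this point is about efficiency only.

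The second reply is that regression adjustment is already foreseen and that covariate lists are commonly left to an analysis plan not shown here. This stands in part. The closing sentence does not exclude baseline adjustment. However, it speaks of unnamed confounders, ties itself to no endpoint, and promises only that adjustment will be evaluated. The same section does name a specific test for these endpoints, and that test has no baseline term.

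The third reply is that the three variables differ. This also stands:

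- PEEP is carried over from entry, so the case is clearest there.
- PSV level is set to targets after randomisation, so its link to the baseline level is not assured.
- Oxygenation index conventionally needs mean airway pressure, which is not among the baseline items named. That list gives examples only, so it may have been recorded.

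A reader might go further and infer that most of the spread on days 1–3 is inherited from baseline, or that adjustment would make 258 patients act like 258/(1 − rho²) = 344, 506 or 717 at rho 0.5, 0.7 or 0.8. The documents support neither. They give no correlation, adjustments accumulate over three days, and patients who are extubated or on controlled ventilation have no PSV level to analyse, so not all 258 would contribute. The equivalent sizes in the table above share that last limit.

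A reader might also take the signed rank test, which is a paired test, as a sign that change from baseline is intended. The Secondary endpoints section describes a comparison between the two arms, so that reading does not fit. The choice of a paired test for independent groups is a separate matter.

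**Conclusion.** The point holds as a recommended improvement to a valid analysis of secondary endpoints. The named tests ignore baseline values that are collected before randomisation, and any non-zero correlation means lost precision. The loss is 9%, 25% or 49% of the variance at an assumed rho of 0.3, 0.5 or 0.7, and the matching power for a 0.25 SD difference is about 56%, 64% or 80% against 52% unadjusted. These figures rest on the assumed rho, a two-sided 5% test and complete data at 129 per arm. The gain is likely to be greatest for PEEP, is less certain for PSV level, and shrinks from day 1 to day 3. The primary non-inferiority test and its 129 per arm are untouched.

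**What to change.** Add to Statistical analysis that the main analysis of PSV level, PEEP and oxygenation index on days 1–3 is a linear model with arm and the pre-randomisation value of the same variable. This can be an ANCOVA for each day or one repeated-measures model over the three days. Report the adjusted difference with its 95% CI, and use ranks or a robust standard error where the distribution is skewed.

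For oxygenation index, use baseline PaO2/FiO2 as the covariate if baseline mean airway pressure was not recorded; the ratio is needed to judge eligibility, so it should be available. FiO2 is titrated between enrolment and the sigh test, so state whether the baseline reading is from before or after that titration. Either is valid, since both precede randomisation.

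The cost is one or two sentences, fixed before the outcome data are compared by arm. It needs no new measurement, no extra patients and no change to the primary analysis.

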### End of follow up

Enrolled patients will be observed until day 28, ICU discharge or death, whichever comes first.

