### Sample size

The sample size was computed based on the hypothesis that PSV + sigh might decrease the rate of failure of assisted ventilation compared to standard PSV. Based on previous data [21], the expected proportion of failure in patients undergoing PSV will be 22% and we hypothesized a proportion of 15% for patients in the PSV + sigh group. Assuming non-inferiority of PSV + sigh treatment, with a tolerance of 5% we estimated that a sample size of 258 patients (with 129 patients per study arm) will be sufficient to assess feasibility of the PSV + sigh strategy in this pilot phase with power of 0.8 and alpha 0.05.

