## Discussion

PROTECTION is a pilot randomized controlled trial to test the long-term clinical feasibility of the addition of sigh to PSV in comparison to standard PSV. If positive, it will provide the basis for a future larger trial aimed at verifying the impact of PSV + sigh on a composite outcome endpoint including 28-day survival and ventilator-free days. Moreover, it will provide physicians a physiologically sound addition (i.e., sigh) to standard PSV for lung protection able to favor assisted ventilation.

Mortality remains considerably high (around 40%) in intubated patients with AHRF [6]. The clinical severity of lung injury at presentation and early appropriate treatment are the main determinants of patients’ outcomes [19]. However, while the lungs recover, VILI might significantly impact survival [1]. Recent studies testing strategies that enhance lung protection (e.g., early referral to an extracorporeal membrane oxygenation (ECMO) center [22]; use of muscle relaxants during the first 48 h after intubation [23]; early use of extended sessions of prone positioning [24]) yielded significantly decreased mortality. However, such trials enrolled only the most severely ill patients with AHRF on controlled mechanical ventilation. A recent large observational study [6], instead, showed that most ventilated patients admitted to the ICU have mild to moderate AHRF or ARDS that leads to considerably high mortality (≈ 35%) anyway. Moreover, the same study reported that around 30% of invasively ventilated patients with AHRF and ARDS are on some form of spontaneous breathing from day 1 after intubation, independent of the severity of their illness [6], and this proportion likely increases within 1 week. Thus, there is an urgent need for interventions that increase lung protection during assisted ventilation.

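### Kaplan-Meier for time to death or extubation ignores death as a competing event: it either overstates extubation or merges a good and a bad outcome in one curve

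*Protocol article*

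**What the plan says.** The only time-to-event statement in the protocol article is in Statistical analysis: "Time to death or extubation will be analyzed using Kaplan-Meier survival curves". The sentence after it reads "Adjustement for potential confounding factors will be evaluated using appropriated regression models", which concerns confounding and not competing events. No cumulative incidence function, cause-specific model or subdistribution model appears anywhere in the article.

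Three other places bear on the point:
- Secondary endpoints lists, among the clinical outcomes, "28-day mortality; ventilator-free days; PSV level, PEEP value and oxygenation index on day 1–3". Time to death or extubation is not in that list.
- End of follow up says "Enrolled patients will be observed until day 28, ICU discharge or death, whichever comes first". Data collection adds: "We will collect data on day 28 for all enrolled patients on mortality, extubation that occurred outside the ICU and readmission to ICU".
- The Discussion gives background mortality: "Mortality remains considerably high (around 40%) in intubated patients with AHRF", and, for the milder majority, "mild to moderate AHRF or ARDS that leads to considerably high mortality (≈ 35%) anyway".

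**The concern.** Death before extubation makes extubation impossible, so it is a competing event and not ordinary loss to follow-up. The sentence can be read in two ways, and Kaplan-Meier serves extubation badly under both.

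1. **Two analyses, with deaths censored in the extubation analysis.** Censoring treats a patient who died as someone who would later have been extubated at the rate of those still ventilated. One minus Kaplan-Meier is then too high as a probability of extubation.
2. **One composite event.** An arm can climb faster because more patients come off the ventilator or because more patients die. The curve cannot tell these apart.

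What is at stake is the description of liberation from ventilation. The Background and Discussion hope that sigh will affect both duration of ventilation and mortality. Unequal mortality between arms is therefore a possibility that the investigators themselves entertain.

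**Working it through.** **The plan's own figure.** The article gives no figure for the time-to-event analysis. Its only computed figure is the sample size, which reproduces. On the success scale (0.78 vs 0.85), with a margin of 0.05, one-sided alpha 0.05 and power 0.80:

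(1.645 + 0.842)² × (0.78×0.22 + 0.85×0.15) / (0.07 + 0.05)² = 6.183 × 0.2991 / 0.0144 = 128.4, so 129 per arm.

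This rests on the binary primary endpoint and neither supports nor weakens the present point.

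**Inputs for the check.** The article gives neither the proportion dying before extubation nor the proportion still ventilated at day 28. Both are assumptions: death before extubation D = 10–35%, still ventilated s = 5–15%, with constant cause-specific hazards over 28 days. The true cumulative extubation is E = 1 − D − s.

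**Formulas.**
- Total cumulative hazard to day 28: H = −ln(s).
- Extubation share of it: H_E = H × E/(E + D).
- One minus Kaplan-Meier with deaths censored: 1 − exp(−H_E).
- Overstatement: 1 − exp(−H_E) − E.

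**Worked case**, D = 25%, s = 10%, E = 65%: H = −ln(0.10) = 2.303. H_E = 2.303 × 0.65/0.90 = 1.663. One minus Kaplan-Meier = 1 − exp(−1.663) = 81.0%, against a true 65.0%.

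| Death before extubation | Still ventilated, day 28 | True extubated | 1 − KM, deaths censored | Overstatement (points) |
|---|---|---|---|---|
| 10% | 15% | 75.0% | 81.2% | 6.2 |
| 10% | 10% | 80.0% | 87.1% | 7.1 |
| 20% | 10% | 70.0% | 83.3% | 13.3 |
| 25% | 10% | 65.0% | 81.0% | 16.0 |
| 30% | 10% | 60.0% | 78.5% | 18.5 |
| 35% | 10% | 55.0% | 75.5% | 20.5 |
| 35% | 5% | 60.0% | 84.9% | 24.9 |

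The first and last rows are the extremes of the assumed grid.

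**Direction.** The cumulative incidence weights each extubation hazard increment by the probability of being alive and still ventilated. One minus Kaplan-Meier weights it by the larger probability of merely not being extubated. It is therefore never below the cumulative incidence, and it exceeds it once deaths precede later extubations. This does not depend on constant hazards; only the size does.

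**Between arms.** Take one arm with 15% death and 75% extubated, and another with 35% death and 55% extubated, each with 10% still ventilated.
- True gap in extubation: 75 − 55 = 20 points.
- Gap in the death-censored curves: 85.3 − 75.5 = 9.8 points.
- Composite curve: 75 + 15 = 90% and 55 + 35 = 90%. With the same total hazard of 2.303, the two curves coincide throughout.
- Cause-specific hazard ratio for extubation: 0.55/0.75 = 0.73. For death: 0.35/0.15 = 2.33. Both remain interpretable.

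**The case against.** The strongest reply is that the sentence is incomplete and not demonstrably wrong. The article does not say that deaths are censored at the time of death. If they were kept in the risk set to day 28 as never extubated, and there were no other censoring, one minus Kaplan-Meier would equal the cumulative incidence. Event and censoring rules are often left to an analysis plan, and none is shown here. What stands of this is that one cannot say which reading was intended. But the article does fix the method, the harmless handling is not stated, and each of the other two readings gives a curve that misleads about extubation.

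Four stronger inferences may tempt a reader, and the article does not support them.
- **The death curve is biased by censoring at ICU discharge.** The End of follow up section might suggest this. However, Data collection obtains day-28 mortality for all enrolled patients, 28-day mortality is a listed outcome, and Statistical analysis nowhere says that patients are censored at discharge. A Kaplan-Meier curve for death alone is sound on those data.
- **The comparison of arms is invalid whenever mortality differs.** This is too broad. A cause-specific hazard contrast, estimated from the same death-censored data, keeps its meaning. The distortion concerns the curves read as extubation probabilities.
- **These curves will drive the larger trial.** The article makes the pilot as a whole the basis for that trial and does not tie these curves to its planning. Ventilator-free days and days on assisted ventilation also describe liberation.
- **The 35–40% mortality can be fed into the table.** Those are background figures. They are not death before extubation in this trial, whose eligibility criteria exclude the sickest patients. Deaths after successful extubation do not compete with it.

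**Conclusion.** The point holds for the extubation part of the analysis. With deaths censored, the absolute extubation curve is too high in both arms, by about 6 to 25 points under constant hazards, 10–35% death before extubation and 5–15% still ventilated at day 28. If mortality is similar in the two arms, both curves are inflated to a similar degree. If it differs, the gap between them misstates the difference in extubation probability. Read as a composite, the curve can hide opposite mixes of death and extubation altogether. The size rests on the assumed rates; the direction does not.

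The consequence is limited. This is a supportive analysis outside the listed secondary endpoints, and it touches neither the primary comparison nor the sample size. It should be corrected because a better method is available at almost no cost.

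**What to change.** Replace the sentence with two separate analyses.

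1. **Extubation.** Analyse time from randomization to successful extubation, or separation from the ventilator for tracheostomized patients, by cumulative incidence (Aalen-Johansen). Death before separation is the competing event. Compare arms by Gray's test and give cause-specific hazard ratios for extubation and for death before it.
2. **Death.** Analyse time from randomization to death by Kaplan-Meier to day 28 in all randomized patients, using the day-28 vital status described in Data collection, with no censoring at extubation or ICU discharge.

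The cost is a change of wording and slightly more analysis work. Design, sample size and primary analysis stay as they are. The daily records and the day-28 follow-up already cover the events. It is worth confirming that dates are recorded for deaths and extubations after ICU discharge, since the article does not say so and both curves need them.
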